#### Levels of Tailoring

The behaviour change modules are tailored based on three levels. First, the intervention components are based on users’ preferences [10]. Participants can choose to enter one or more components per session. Second, the feedback messages are tailored to participants’ characteristics – gender, age, COPD status and level of disability. Participants’ names are used to personalize messages. Third, the feedback messages are tailored to key behaviour determinants based on psychosocial constructs. Examples of key behaviour determinants are: barriers to quitting smoking and plans to overcome them, perceived social support to be physically active, pros and cons of smoking cessation specified by participants and action plans participants make to start being more physically active.

#### Website

The behaviour change modules are embedded in a website, which can be accessed through a personal account. To keep the length of feedback messages as short as possible, the messages refer to background information and tools available via the website. The website contains background information about the MasterYourBreath project, COPD, risk for COPD, smoking and physical activity using written information, illustrations, videos and hyperlinks to other informative websites. In addition, videos of exercises that can be done at home are also included. New content will be added to the website once a month. This includes an interview with a COPD patient about coping with smoking and physical activity in her daily life and stories based on behavioural journalism to prompt participants to visit the behaviour change modules. Behavioural journalism promotes behaviour change by presenting peer modelling for cognitive processes that result in behaviour change [40]. Problems and reasons for participants choosing not to use the intervention that are communicated to the research team are leveraged to create the behavioural journalism stories in order to encourage the use of the behaviour change modules.

#### Prompts to promote technology use

The web-based intervention can be used ad libitum. Prompts will be sent to the experimental group to boost intervention use [41] with a two week time interval and some referring to new content on the website, since this may increase the number of follow-up visits [42].

If participants do not use at least one of the behaviour change modules within two weeks, they receive a prompt by e-mail to login to the website and visit a behaviour change module. Another prompt is sent out two weeks after the first prompt if participants fail to visit a behaviour change module. If participants use a behaviour change module, they receive a prompt to use the intervention again every month. This means that if participants visit both behaviour change modules, they receive a prompt every two weeks. Prompts are tailored for COPD or people at risk for COPD and refer to intervention components, new stories on the website and possible current problems with behaviour change, such as physical activity during the winter season. Participants can click on a personalised link embedded in the e-mail to access the website without having to log in.

### Data collection

A self-administered web-based questionnaire will be deployed at baseline and after 6 months. All outcome measures will be collected through this questionnaire, except for the demographic characteristics in the group that is recruited online. Flycatcher members enter their demographic variables when they start their membership. These variables are updated annually.

#### Demographic characteristics

Demographic variables include: gender, age, height, weight, country of birth, mother’s country of birth, father’s country of birth, marital status (single; in a relationship/living together; married; divorced; widowed), living situation (with parents or caregivers; alone; with partner without child(ren); with partner and child(ren); without partner with child(ren); with other people), housing (property is bought by one of the household members; property is rented by one of the household members), education level (recoded into three categories: ‘low’ (1) = primary school/basic vocational school; ‘medium’ (2) = secondary vocational school/high school degree and ‘high’(3) = higher professional degree/university degree), current work status (employed by the government; employed, but not by the government; temporary worker; self-employed; not employed), number of work hours a week (36 or more/20 to 35/12 to 19/less than 12), function (management function/non-management function), number of people managing directly and indirectly, and household income (minimum, less than 11.000 euro’s a year; less than average, between 11.000 and 23.000 euro’s a year; average, between 23.000 and 34.000 a year; 1–2 times average 34.000 to 56.000 euro’s a year; 2 times average or more 56.000 euro’s or more a year; do not know/do not want to tell).

#### Smoking

Participants are asked if they have ever smoked. Current smoking behaviour is measured by asking participants if they smoke, what they smoke (cigarettes, rolling tobacco, cigars or pipe tobacco) and how much they smoke. Questions assessing 24-hour and 7-day point prevalence abstinence (i.e., “Did you smoke during the past 24 hours, even if it was just 1 puff?” Yes; No “Did you smoke the past 7 days, even if it was just 1 puff?” Yes; No) are incorporated. To assess continued and prolonged abstinence [43] we first ask when the participants’ last serious quit date was and then measure continued abstinence (“Have you smoked since this quit date?” No, not a puff; Yes, 1–5 cigarettes or other tobacco products; Yes, more than 5 cigarettes or other tobacco products) and prolonged abstinence, allowing a grace period in which smoking behaviour will not be counted as such (“Have you smoked since two weeks after your quit date?” No, not a puff; Yes, 1–5 cigarettes or other tobacco products; Yes, more than 5 cigarettes or other tobacco products). Moreover, a question assessing the number of quit attempts, a question measuring which type of smoking cessation aids are used and the 6 item version of the Fagerström Test for Nicotine Dependence [44] are included.

#### Physical activity

Level of physical activity will be measured by the short version of the International Physical Activity Questionnaire (IPAQ) [45].

#### Health status

Participants will be asked if they are diagnosed with COPD, when they were diagnosed and if they suffer of any other chronic disease. The severity of COPD will be measured according to the standards defined by the Global Initiative for Chronic Obstructive Lung Disease (GOLD) [46]. Furthermore, the Medical research council (MRC) Dyspnoea score [47] will be administered to measure the level of disability [48].

#### Quality of life

COPD related quality of life will be measured by the Clinical COPD Questionnaire (CCQ) [49].

#### Stages of change

The stage of change [50] will be assessed for smoking (“Did you quit smoking?” Yes, I quit more than 6 months ago; Yes, I quit within the last 6 months; No, but I plan to quit within the next 30 days; No, but I plan to quit within the next 3 months; No, but I plan to quit within the next 6 months; No, and I do NOT plan to quit within the next 6 months). And physical activity (“Are you engaged in medium and/or intense physical activity for at least 30 minutes a day, 5 days a week?” Yes, since 6 months or longer; Yes, since less than 6 months; No, but I plan to be within the next 30 days; No, but I plan to be within the next 3 months; No, but I plan to be within the next 6 months; No, and I do NOT plan to be within the next 6 months).

#### Intention to change behaviour

The intention to change smoking behaviour will be measured on a 7 item likert scale (I certainly plan to quit smoking – I certainly do not plan to quit smoking) and another question measures the intention to change physical activity (I certainly plan to be more physically active – I certainly do not plan to be more physically active).

### Primary and secondary outcomes

One primary outcome measure per module is defined, including the 7-day point prevalence abstinence measuring smoking cessation and the short version of the IPAQ measuring the level of physical activity. Secondary outcomes are alternative smoking behaviour outcomes (i.e., current smoking behavior, 24-hour point prevalence abstinence, prolonged abstinence, continued abstinence and number of quit attempts), dyspnoea score, COPD related quality of life, stages of change and intention to change behaviour.

### Process evaluation

The process evaluation will be carried out in line with a framework provided by Saunders et al. [51] to examine the implementation of the MasterYourBreath study protocol and the relationship between specific intervention components and outcomes. The implementation of the study protocol will be monitored and documented by the research team. Quantitative data will be collected for program use, for example login frequency and frequency of use of each intervention component. The web-based questionnaire, will be used to ask participants of the intervention group, who did not use the intervention, to provide a reason for this (not enough time; not necessary, because I live healthy; not necessary, because I think I am not at risk for or do not have COPD; I wanted to visit the website, but I could not login to the website; other reason). Participants who used the intervention will be asked questions largely based on earlier work of de Vries et al. [11] about the website’s navigation (1 item; i.e., “It was easy to find information on the website” totally agree – totally disagree) the level of personalisation, novelty, comprehensibility and usefulness of the feedback messages (4 items; e.g., “the feedback messages were personally relevant to me” totally agree – totally disagree) and two general questions (i.e., “I would recommend MasterYourBreath to others” totally agree – totally disagree “I would like to use MasterYourBreath in the future” totally agree – totally disagree). Finally, participants will be asked to rate the feedback messages on a scale from 1 – 10. Semi-structured interviews will be conducted with participants of the experimental group to explore their reasons for participation, expectations of the study, experiences with the intervention and e-mail prompts, the recruitment procedure and information regarding the project. The interviews will be conducted after participants finish the follow-up questionnaire at 6 months, in order to avoid the contamination of the measurement. To create a heterogeneous sample, participants will be selected based on recruitment strategy (online or general practice), age, gender, COPD patient/at risk for COPD, education level, current work status and smoking status. A researcher not involved in other aspects of the study will conduct, audiotape and transcribe the interviews verbatim.

Besides, all communication between participants and the research team will be documented.

### Analysis

Number (%) and mean (SD) will be computed for categorical and numerical baseline characteristics, respectively, where the differences in these characteristics are assessed between intervention and control groups by chi-square or Fisher’s exact tests for categorical variables and independent-samples t-tests for numerical variables. Data will be analysed according to the intention to treat principle. In addition, a per-protocol analysis will be conducted. For this analysis, it is required that participants complete at least one intervention component. The uncorrected and corrected effect of the intervention on the primary and secondary outcome measures at 6 months will be assessed with logistic regression for categorical outcomes and linear regression for numerical outcomes. As for correction, baseline characteristics related to the outcome at 6 months are included in the regression model to increase the precision of the intervention effect. Since randomisation is stratified by recruitment method (online or through general practices), recruitment method is also included as a covariate in these analyses. As a sensitivity analysis, the differences in baseline characteristics between the groups recruited online and through the practices are compared. If this analysis shows that the groups are comparable, the analyses will be applied to the whole dataset, otherwise the groups will be analysed separately.

Quantitative process evaluation data will be analysed using descriptive statistics, such as number (%) and mean (SD). Differences in intervention use and satisfaction with the intervention between specific subgroups, such as gender, smoking/non-smoking and age groups, will be analysed. Content analysis will be performed to analyse the qualitative process evaluation data using the constant comparative method [52]. Statistical analysis will be performed using Statistical Package for Social Sciences (SPSS) version 19.

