**Methods/Design:**

This paper presents the protocol of a randomised controlled trial testing the effectiveness of a web-based, computer-tailored self-management intervention to change health behaviours of people with or at risk for COPD. An intervention group will be compared to a usual care control group, in which the intervention group will receive a web-based, computer-tailored self-management intervention. Participants will be recruited from an online panel and through general practices. Outcomes will be measured at baseline and at 6 months. The primary outcomes will be smoking behaviour, measuring the 7-day point prevalence abstinence and physical activity, measured in minutes. Secondary outcomes will include dyspnoea score, quality of life, stages of change, intention to change behaviour and alternative smoking behaviour measures, including current smoking behaviour, 24-hour point prevalence abstinence, prolonged abstinence, continued abstinence and number of quit attempts.

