## Discussion

This paper presents the design of a randomised controlled trial, testing the effectiveness of a computer-tailored intervention on the self-management of people with or at risk for COPD. To our knowledge, only limited research has been conducted to evaluate self-management interventions for COPD patients [3] and none of these studies used computer-tailored technology. The results of this study explore the potential benefit of using computer-tailored technology to improve self-management related health behaviours of people at risk for COPD, in addition to those with COPD.

Individuals at risk for COPD are less likely to be offered a self-management intervention by a health care provider, but they can be reached relatively easily through the internet and health behaviour change can be promoted. We also expect that including people at risk for COPD and recruiting some of the participants online increases the likelihood of assuring adequate power.

The choice for a hybrid sample of participants recruited by two methods (online panel and general practice) was made after considering the results of the pilot study (unpublished observations). In the pilot study participants were recruited by a primary care practice nurse during a yearly consultation for routine monitoring of their chronic condition. This recruitment strategy resulted in an insufficient number of participants. Not all eligible patients were invited by the nurses and many patients declined participation. We concluded that it is not feasible to recruit 446 participants per arm using this approach. Therefore, we choose to recruit participants from an online panel and through general practices by sending an invitation letter to every eligible patient.

A possible threat to this study is that large numbers of participants might not use or discontinue to use the intervention, which is common in e-Health interventions [53]. If a large percentage of participants opt not to use the intervention, an intention to treat analysis could underestimate the intervention effect [54]. For this reason we will conduct a per-protocol analysis following an intention to treat analysis.

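### The per-protocol analysis compares self-selected users with all controls, so it replaces dilution with a selection bias of unknown size and direction

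*Protocol article*

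**What the plan says.** The Analysis section sets the main approach: "Data will be analysed according to the intention to treat principle". It then adds a per-protocol analysis with a single criterion: "For this analysis, it is required that participants complete at least one intervention component". No matching criterion for controls and no method for handling selection is given.

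The Discussion explains the purpose. It warns: "If a large percentage of participants opt not to use the intervention, an intention to treat analysis could underestimate the intervention effect". It continues: "For this reason we will conduct a per-protocol analysis following an intention to treat analysis".

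Three other places bear on how the rule works:

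- Abstract, Methods/Design: "An intervention group will be compared to a usual care control group, in which the intervention group will receive a web-based, computer-tailored self-management intervention". Only one arm has components to complete.
- Prompts to promote technology use: "The web-based intervention can be used ad libitum". Use is the participant's choice.
- Process evaluation: the answer options for not using the website include "not necessary, because I live healthy", as well as lack of time, not seeing oneself as at risk, a login failure, and an open category.

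Both uncorrected and corrected models are planned. For the corrected ones, "baseline characteristics related to the outcome at 6 months are included in the regression model to increase the precision of the intervention effect".

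**The concern.** Read literally, the criterion would leave no controls, because none of them can complete a component. The only workable reading is that it removes non-users from the intervention arm and keeps every control. Randomisation does not protect that comparison: the controls still include the people who would not have used the website, and the intervention group no longer does.

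If would-be users and non-users differ in their chance of abstaining, or in how active they would be anyway, the contrast differs from zero without any intervention effect. The bias can go either way. Motivated users would inflate the result. Non-users who stay away because they already live healthily would deflate it, most plausibly for physical activity.

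What is at stake is interpretation. Since the Discussion presents this analysis as the response to a diluted ITT estimate, a null ITT result beside a positive per-protocol result could be taken as efficacy among users, which this contrast cannot establish.

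**Working it through.** **1. The plan's own figures.** Inputs from Sample size calculation: 20% v 10% abstinence, 80% power, significance level 0.05, 49.2% smokers. A two-sided test of two proportions gives 199 smokers per arm, or 219 with continuity correction. 219 / 0.492 = 445.1, rounded up to 446, as stated. For physical activity (SD 26.63, difference 10 minutes) the usual formula gives 112 per arm, as stated. Neither figure is in dispute; 219 smokers per arm is used below.

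**2. Assumptions.** The protocol gives neither of these, so a range is shown:

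- u, the share of the intervention arm completing at least one component: 0.3 to 0.7.
- r, the ratio of abstinence without intervention in would-be users to that in non-users: 0.5 to 3.

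**3. No true effect, 10% abstinence overall.** Non-users abstain at p_n = 0.10 / (u r + 1 - u), and users at p_u = r p_n. The per-protocol difference is p_u - 0.10. The rejection rate is for an unadjusted two-sided 5% pooled-variance test of 219u users against 219 controls.

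Example: u = 0.3, r = 3 gives p_n = 0.10 / 1.6 = 0.0625, p_u = 0.1875, difference +0.0875.

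| u | r | Users | Spurious difference (points) | Rejection rate |
|---|---|---|---|---|
| 0.3 | 0.5 | 5.9% | -4.1 | 14% |
| 0.3 | 2 | 15.4% | +5.4 | 25% |
| 0.3 | 3 | 18.8% | +8.8 | 48% |
| 0.5 | 0.5 | 6.7% | -3.3 | 15% |
| 0.5 | 2 | 13.3% | +3.3 | 16% |
| 0.7 | 1.5 | 11.1% | +1.1 | 7% |
| any | 1 | 10.0% | 0 | 5% |

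**4. True effect of +10 points in users, none in non-users.** The ITT difference is 10u: 3, 5 and 7 points at u = 0.3, 0.5 and 0.7. The per-protocol difference is (p_u + 0.10) - 0.10 = p_u, so it runs from +5.9 to +18.8 points over the grid and equals +10 only at r = 1. The complier-average estimate, ITT / u, is 10u / u = +10 for every r.

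**5. Physical activity, no true effect.** If users and non-users differ by g minutes, the bias is (1 - u) g. With u = 0.5 and g = 10 it is 5 minutes, half the 10-minute target. With g = -10 it is -5 minutes.

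**6. What the complier estimate assumes.** Suppose being assigned to the website arm shifts abstinence by d points in people who complete no component. Then ITT / u = 10 + d (1 - u) / u. With d = 1 (assumed), that is 11.0 at u = 0.5 and 12.3 at u = 0.3. The estimate is too large if prompts or website content help non-users.

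**The case against.** **ITT stays the main analysis.** This stands. The per-protocol analysis is additional and follows ITT, so the randomised comparison and the sample size are untouched. A reader might infer that the trial's main conclusion is compromised; nothing in the protocol says the per-protocol result would override ITT.

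**The reasons for non-use are answer options, not data.** This stands. A reader might infer that the list proves use is prognostic. It only makes that plausible, and lack of time or a login failure need not be prognostic. The option about already living healthily suggests non-users with a better prognosis, so the documents do not support reading the bias as necessarily favourable to the intervention.

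**The corrected models may help.** This stands in part. Nicotine dependence, stage of change and intention are measured at baseline and may capture some of the selection. But covariates are chosen for their relation to the outcome, with precision as the stated aim, and unmeasured motivation would remain. It is therefore too strong to say that the analysis cannot correct dilution at all; it cannot be relied on to do so.

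**An article may leave analysis sets to a fuller document.** This stands for details, such as whether a component must come from the module that matches the outcome. As worded, a component of either module qualifies, but a per-module reading is open because the primary outcomes are defined per module. It does not remove the main point: the stated criterion applies only to one arm, and the Discussion states what the resulting contrast is for.

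**The complier-average estimate has its own weakness.** This stands. Participants who complete no component can still receive prompts and view website information, videos and stories.

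**Conclusion.** The point holds. The rule as written compares self-selected users with all controls, and that contrast estimates the effect in users only if use is unrelated to prognosis. Under no true effect the spurious difference in abstinence runs from about -4 to +9 points against a planned 10. That range rests on assumed uptake of 30% to 70% and an assumed user to non-user ratio of 0.5 to 3, without covariate correction; with high uptake and mild selection it is close to 1 point.

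This should be fixed, but it is an improvement to a supplementary analysis and not a threat to the main result.

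**What to change.** - Keep ITT as the main analysis.
- Estimate the effect in users as a complier-average causal effect on the risk-difference or mean-difference scale, with randomisation as the instrument. Non-compliance is one-sided because controls have no access, and use of each component is already to be recorded under Process evaluation.
- Take completion of any component as the main definition of exposure. Report module-specific exposure as a sensitivity analysis, since it also assumes that the other module has no effect on the outcome.
- State that prompts and website content reaching participants who complete no component could violate the exclusion assumption and, if they help, make the estimate too large.
- If the user-versus-control comparison is kept, label it non-randomised and exploratory. Remove the implication in the Discussion that it corrects ITT underestimation.

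The cost is some wording and one extra model, with no new data. Intervals will be wider than those of the user comparison: the standard error is roughly that of the ITT estimate divided by u, so about double at 50% uptake. The method does not restore power lost to non-use.

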#### Sample size calculation

The sample size for smoking is based on the assumption that 49.2% of the population with an increased COPD risk smokes [22]. A sample size calculation by PS software [23] indicates that 446 participants will be necessary in each arm at the end of the trial to detect 20% 7-day point prevalence abstinence in the intervention group, compared to 10% in the control group [24], with a 80% power and a significance level of 0.05. Since we do not uphold an upper bound for minutes a person can be physically active, 100% of the participants will be included in the analyses for physical activity. In another study the standard deviation for the Dutch population was 26.63 [25]. Considering this, we will need 112 participants in each arm, which is feasible to obtain from the suggested sample of 446 participants in order to detect a difference of 10 minutes with 80% power and a 0.05 significance level.

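### The per-protocol rule filters only the intervention arm on a self-chosen behaviour, so it can be biased in either direction and should not be offered as the answer to dilution by non-use

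*Protocol article*

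**What the plan says.** The protocol article (Analysis) makes intention to treat the stated analysis and adds a per-protocol analysis with this entry rule: "For this analysis, it is required that participants complete at least one intervention component". It does not say which controls are kept.

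The Discussion gives the purpose. If many participants do not use the intervention, intention to treat could understate its effect, and "For this reason we will conduct a per-protocol analysis following an intention to treat analysis". Selection of users is not mentioned there.

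Other sections bear on the point:
- Study design: controls receive usual care.
- Website: the modules sit in a site "which can be accessed through a personal account".
- Levels of Tailoring, and Prompts to promote technology use: participants use the site as much or as little as they like and choose which components to enter.
- Process evaluation: logins and use of each component are recorded.
- Analysis: uncorrected and corrected models are both run. The stated aim of correction is precision.

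**The concern.** Completing a component is a choice made after randomisation, and only one arm can make it. The rule removes non-users from the intervention arm, while the control arm still contains the people who would not have used the site. If users and non-users differ in prognosis, the two groups differ before the website has done anything.

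At a given prognosis gap the bias grows with the share of non-users. Widespread non-use is the situation for which the Discussion introduces the analysis. A reader who meets a small intention-to-treat effect beside a larger per-protocol effect would take the second as the undiluted effect, when part or all of it may be selection.

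**Working it through.** **Inputs from the Sample size calculation section.** The smoking target is "to detect 20% 7-day point prevalence abstinence in the intervention group, compared to 10% in the control group", "with a 80% power and a significance level of 0.05". The share of smokers is "49.2% of the population with an increased COPD risk smokes" and the size is "446 participants will be necessary in each arm at the end of the trial". For activity, "the standard deviation for the Dutch population was 26.63", and the target difference is 10 minutes.

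**The plan's own figures.** Two proportions, 20% v 10%, two-sided 0.05 (two-sided is assumed), 80% power: 199 per arm without continuity correction and 219 with it. 219 / 0.492 = 445.1, rounded up to 446, which matches. Two means, difference 10, SD 26.63: 112 per arm, which matches. So 446 per arm means about 219 smokers per arm.

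**Assumptions, not in the article.** Share of users u = 0.3, 0.5 or 0.7; ratio r of abstinence in would-be users to would-be non-users = 1.5, 2 or 3; no website effect. All figures are for the unadjusted comparison of users with all controls.

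**Smoking.** Overall abstinence is 10% in both arms. The non-user rate is b = 0.10 / (u·r + 1 − u) and the user rate is a = r·b. The false difference is d = a − 0.10. With SE0 the pooled and SE1 the unpooled standard error, the chance of a significant result in favour is 1 − Φ((1.96·SE0 − d) / SE1).

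Example, u = 0.5 and r = 3: b = 0.10 / 2 = 5%, a = 15%, with 109.5 users against 219 controls. d = 0.05, SE0 = 0.0376, SE1 = 0.0397. (1.96 × 0.0376 − 0.05) / 0.0397 = 0.60, giving 27.6%.

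| Use | r = 1.5 | r = 2 | r = 3 |
|---|---|---|---|
| 30% | 11.8% | 24.8% | 48.4% |
| 50% | 8.5% | 15.6% | 27.6% |
| 70% | 5.5% | 8.1% | 11.8% |

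The nominal value is 2.5%.

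A separate simulation (200,000 trials per scenario) set the user to non-user contrast as an odds ratio. An odds ratio of 3 gave 24.3% at 50% use and 40.2% at 30%. These are a little lower because a rate ratio of 3 (15% v 5%) is an odds ratio of about 3.4. With an odds ratio of 1 there was no bias. With 0.5 at 50% use the shift was −3.0 points, with false harm in 13.1% of trials.

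**Activity.** If users differ from non-users by D minutes anyway, the shift is (1 − u)·D and SE = 26.63 × √(1/446 + 1/(446u)). At u = 0.5, SE = 2.18:
- D = 2.5: shift 1.25 minutes, 8.3% false benefit.
- D = 5: shift 2.5 minutes, 20.7%.
- D = 10: shift 5 minutes, 62.9%.

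Reversing the sign of D gives the same percentages as false harm.

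**Complier average causal effect (CACE) in the same null simulations.** The intention-to-treat difference divided by the share of users was centred on zero (within 0.1 point) in every scenario. Three limits apply:
- Precision: its SD was 9.7, 5.8 and 4.1 points at 30%, 50% and 70% use.
- Power: with a 10-point effect in users only, intention-to-treat power is 16%, 35% and 57% at those levels of use, and CACE power is essentially the same.
- Exclusion restriction: if allocation alone moves non-completers by e, the bias is e(1 − u)/u. For e = 2 points this is 4.7, 2.0 and 0.9 points at 30%, 50% and 70% use.

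**The case against.** **The per-protocol analysis is additional.** Intention to treat is the stated analysis and no primary conclusion is tied to the other one. This stands. A reader might infer that the trial's main result is compromised; it is not. What remains is that the article fixes both the rule and its purpose, so this is not a detail merely left to a fuller document.

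**The direction is not known.** A reader might infer that this analysis will show a benefit even if the website does nothing. The article does not support that. It has no data on how users differ from non-users, and with equal prognosis there is no bias. Among its listed reasons for non-use (Process evaluation) is that the respondent already lives healthily, which would make non-users the better group, most plausibly for activity. Even in the largest smoking cell a false benefit occurs in under half of trials.

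**The corrected model may help.** Intention, stage of change, nicotine dependence and activity are all measured at baseline and may be among the covariates. If users are simply more active at the start, adjustment could remove much of that gap. This stands as a reason to expect less bias than the unadjusted figures show. But the covariates are not listed, correction is aimed at precision, and motivation need not be fully captured.

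**The complier estimate has its own weak point.** A reader might infer that it is free of bias. It is so only if allocation does nothing for those counted as non-users. Non-users receive e-mail prompts, and the site offers information, stories and exercise videos outside the components. Someone who uses these, or leaves a component unfinished, counts as a non-user. The objection stands and must be stated with the estimate.

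**The control set is an inference.** The article says neither that all controls are kept nor that controls have no account. Reading the rule as emptying the control arm would be strained. Keeping all controls is the workable reading, since usual care gives controls nothing to complete.

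**Conclusion.** The concern holds in this form: the rule selects on a post-randomisation choice in one arm, so the comparison is not randomised, and the Discussion should not present it as the answer to dilution. The bias can go either way, probably towards benefit for smoking, where users are plausibly the more motivated to quit, and less predictably for activity.

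The size depends on assumed levels of use and assumed user to non-user gaps. Over the smoking range examined, the false-benefit rate is roughly 2 to 19 times the nominal 2.5%; at 70% use it does not exceed 11.8%. Adjustment may lower these figures by an amount that the article does not allow one to compute. The intention-to-treat result is unaffected, so this is a correction worth making rather than a fault in the primary analysis.

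**What to change.** In Analysis and in the Discussion:

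1. Add a complier average causal effect by two-stage least squares, with allocation as instrument for use. Include all randomised participants, handle outcomes as in the intention-to-treat analysis, and adjust for recruitment method and the same baseline covariates. Report a risk difference for abstinence and minutes for activity.
2. State its assumptions: controls have no access; and prompts, website content outside the components and unfinished components have no effect in those counted as non-users. Add a sensitivity analysis that defines use as any login, which helps in part.
3. Label the per-protocol result exploratory, and stop presenting it as the correction for dilution.
4. Say that intention to treat stays the main analysis and that the complier estimate describes the effect in users.

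The cost is wording and a few lines of code; use data are already collected. The downsides are wide intervals when use is low, no power gain over intention to treat, and residual bias if the exclusion restriction fails.
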